## Abstract

**Background:**

Tinnitus is a common chronic health condition that affects 10% to 20% of the general population. Among severe sufferers it causes disability in various areas. As a result of the tinnitus, quality of life is often impaired. At present there is no cure or uniformly effective treatment, leading to fragmentized and costly tinnitus care. Evidence suggests that a comprehensive multidisciplinary approach in treating tinnitus is effective. The main objective of this study is to examine the effectiveness, costs, and cost-effectiveness of a comprehensive treatment provided by a specialized tinnitus center versus usual care. This paper describes the study protocol.

**Methods/Design:**

In a randomized controlled clinical trial 198 tinnitus patients will be randomly assigned to a specialized tinnitus care group or a usual care group. Adult tinnitus sufferers referred to the audiological centre are eligible. Included patients will be followed for 12 months. Primary outcome measure is generic quality of life (measured with the Health Utilities Index Mark III). Secondary outcomes are severity of tinnitus, general distress, tinnitus cognitions, tinnitus specific fear, and costs. Based on health state utility outcome data the number of patients to include is 198. Economic evaluation will be performed from a societal perspective.

**Discussion:**

This is, to our knowledge, the first randomized controlled trial that evaluates a comprehensive treatment of tinnitus and includes a full economic evaluation from a societal perspective. If this intervention proves to be effective and cost-effective, implementation of this intervention is considered and anticipated.

**Trial Registration:**

The trial has been registered at ClinicalTrial.gov. The trial registration number is NCT00733044

## Background

### Problem definition

#### The disease

Subjective tinnitus is the involuntary perception of the concept of a sound without the presence of an external source. It is a chronic condition that is highly prevalent, especially among hearing impaired individuals. Studies show a prevalence of 10% to 20% in the general population [1,2] and among hearing impaired individuals prevalence has been estimated at 75% to 80% [3]. Of the Dutch population at least 2 million individuals suffer from some form of tinnitus, 340.000 individuals indicate to hear the tinnitus continuously and 60.000 individuals claim to be severely impaired in their daily activities [4]. Among severe sufferers it causes disability associated with severe affective problems, major declines in concentration, sleeping difficulties, hypersensitivity to sounds and problems in (re-)directing attention. The combination of these complaints makes them feel exhausted and frustrated resulting in diminished quality of life [5-9]. Tinnitus is known to occur as a concomitant of almost all the dysfunctions that involve the human auditory system [1], and it is postulated that the aetiology of tinnitus is diverse and that different activation circumstances can be present [10]. Little is known about the pathophysiology and there is no known drug or curative therapy at present [11] though considerable research effort has been expended in this regard.

#### The health care problem

In many cases tinnitus sufferers are referred to different caregivers in a non-standardized way, and often receive insufficient and sometimes inappropriate treatment. This may comprise prescribing a drug that is not proven to be effective, or informing the patients that not much can be done to improve the situation. Especially in those individuals suffering from a moderate to severe tinnitus, incorrect information and delay of appropriate treatment is expected to increase psychological strain, aggravation of tinnitus severity, and prolongation of the referral trajectory [11]. Since tinnitus sufferers seek help in various areas of health care without receiving appropriate treatment, they are financially burdening the system superfluously. In absence of a proven cure or uniformly effective treatment, tinnitus care is often fragmentised and costly [12].

#### Usual Care

As for most health problems in the Dutch population, the general practitioner (GP) is the initial professional to consult for patients with tinnitus. In most cases, within six months after onset of subjective tinnitus the individual consults his GP, but one quarter of the respondents wait several years until they seek help [4]. In the official Dutch GP patient information letter on tinnitus (URL: ), it is stated that there is not much that can be done to alleviate complaints. Another frequently consulted specialist is the ENT physician. Treatment possibilities include removal of cerumen, medication, and audiological rehabilitation. Generally, the effects of these treatments are disappointing.

#### Motivation and relevance for the chosen intervention

A recent study by El Refaie et al (2004) shows that functional and social handicap in tinnitus sufferers is significantly reduced, and quality of life improves significantly, as a result of attendance at a specialised tinnitus clinic. Specialised clinics for chronic disorders such as tinnitus and chronic pain have been proven to be most effective in treatment [13]. Similarities between tinnitus and chronic pain in terms of cognitive and behavioural mechanisms [14] have been suggested recently and a similar treatment could be effective for the tinnitus population. As in chronic pain, multidisciplinary specialised treatment is more effective in ameliorating severe tinnitus complaints than monodisciplinary treatments. A retrospective pilot study, by the applicants of this proposal, in the Tinnitus Centre Limburg (TCL) shows significant improvements in 71% of the patients (N = 41). Intrusiveness of the tinnitus ameliorates in 85% of the subjects and 78% experiences improvement in emotional distress caused by the tinnitus.

### Objective

The objective of this study is to examine the effectiveness, costs and cost-effectiveness of a comprehensive multidisciplinary treatment provided by a specialised tinnitus centre. Treatment is based on a stepped care approach, tailored to individual needs, with key elements from cognitive behavioural therapy, education, relaxation techniques, attention diversion, exposure in daily live situations, and tinnitus retraining therapy.

The following research questions were formulated:

1. What are the effects on generic quality of life of comprehensive specialized tinnitus care as provided by a specialised tinnitus centre, as compared to usual care?

2. What are the effects on health, in terms of negative affect, tinnitus beliefs, fear of the tinnitus, and tinnitus annoyance, of comprehensive specialized tinnitus care as provided by a specialised tinnitus centre, as compared to usual care?

3. What are the costs to health care and to society of treatment provided by a specialised tinnitus centre in the Dutch health care system as compared to usual care?

4. What is the cost-effectiveness of treatment provided by a specialised tinnitus centre in the Dutch health care system as compared to usual care?

## Methods/design

### Design

A randomised controlled clinical trial will be performed, with 2 conditions (Fig. 1). Patients will be assigned to a Usual Care (UC) Control condition or a Tinnitus Centre Limburg care (TCL) condition. Both treatment conditions (UC and TCL) will be provided by the Audiological Centre Hoensbroeck. Measures will be taken for blinding patients to treatment assignment.

**Figure 1 F1:**
[figure not shown]
**Flowchart levels of care within randomized controlled clinical trial in Tinnitus Centre Limburg**.

For assessing the cost-effectiveness, the TCL care group will be compared only to the UC group and not to other treatment programs. The analysis will be performed from a societal perspective.

### Participants

The study population consists of tinnitus sufferers referred to the TCL, with subjective tinnitus complaints, aged 18 years and older. Exclusion criterion is not being able to write and read in Dutch.

Inclusion of patients started on September 1^st ^2007 and will proceed until the targeted number of patients is reached, for a maximum of 18 months. It is expected that enough patients will be referred to the TCL during this period to reach the necessary number as was calculated by power-analysis.

### Sample size calculation and feasibility of recruitment

After attending a specialised tinnitus clinic a change of 0.065 in health state utility as measured with the SF-6D has been observed [9]. To detect this difference (assuming a two-sided significance level = 0.05, power = 80%, standard deviation of the difference = 0.15), 86 persons per group are needed. Taking into account 15% loss to follow up, the required sample size is 99 persons per group (198 persons in total).

Approximately 400 individuals suffering from tinnitus apply to TCL yearly. We expect this number to stay stable or even increase in the coming years. Therefore it is expected that it will not be necessary to actively recruit patients for this trial.

### Patient allocation and randomization

Research information in written format and a declaration of willingness to participate in the trial will be sent to all new patients of the Tinnitus Centre Limburg that are registered with subjective tinnitus complaints. If a patient declares that he or she is willing to participate in the study they will be invited for the baseline measurement. This face-to-face contact will be used to determine whether the patients understood the information correctly and a written informed consent will be obtained. If they agree, a hearing test will be performed to determine the level of hearing loss and the patients are asked to fill in the tinnitus questionnaire (TQ) [15] to determine the severity of the tinnitus. Based on the Fletcher Index and the scores on the TQ the patient will be randomly assigned to one of the treatment groups. Since treatment depends on tinnitus severity and the severity of hearing loss it will be important that these two prognostic factors are equally presented in the UC group and the TCL group.

Treatment allocation will be achieved by block randomisation (four blocks; A, B, C & D) to ensure equal and balanced groups. A randomization list was generated using randomization software. An equal number of patients will be allocated to the TCL group and the UC group. Patients with a score equal to or less than 46 on the TQ and a Fletcher Index below 60 dB will be allocated to block A. Patients with a score equal too or less than 46 on the TQ and a Fletcher Index equal to or above 60 dB will be allocated to block B. Patients with a score above 46 on the TQ and a Fletcher Index below 60 dB will be allocated to block C. Finally, patients with a score equal to or below 46 on the TQ and a Fletcher Index above or equal to 60 dB will be allocated to block D. The randomization procedure will be performed by an independent person at a location outside TCL.

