## Discussion

### Potential strengths of the study protocol

#### Design

To our knowledge this is the first randomized controlled clinical trial that evaluates a comprehensive multidisciplinary treatment of tinnitus versus care as usual. A particular strength is the randomization procedure, in which allocation is concealed. Randomization is done at the patient level and stratified on degree of hearing impairment and tinnitus severity. This procedure is performed by an external independent person.

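### Block D of the randomisation rule repeats block B, so patients with TQ above 46 and a Fletcher Index of 60 dB or more have no stratum

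*Protocol article*

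**What the plan says.** The section on patient allocation and randomization explains that treatment depends on tinnitus severity and degree of hearing loss, and that both should therefore be evenly represented in the two arms. It then sets out the mechanism: "Treatment allocation will be achieved by block randomisation (four blocks; A, B, C & D) to ensure equal and balanced groups". The four definitions follow:

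- Block A takes those at or under 46 on the TQ whose Fletcher Index is under 60 dB.
- Block B takes "Patients with a score equal too or less than 46 on the TQ and a Fletcher Index equal to or above 60 dB".
- Block C is worded as "Patients with a score above 46 on the TQ and a Fletcher Index below 60 dB will be allocated to block C".
- Block D takes "patients with a score equal to or below 46 on the TQ and a Fletcher Index above or equal to 60 dB".

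The same section says that the randomisation list had already been produced by software and that someone independent, off site, carries out the procedure. The Discussion, under Design, presents the randomisation as a particular strength and describes it as "stratified on degree of hearing impairment and tinnitus severity".

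**The concern.** Two factors, each cut in two, make four cells, and four blocks are announced. The definition of block D appears to differ from that of block B in phrasing only. If so, one cell has two blocks and another has none.

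The cell at risk is the one above the cut-off on both factors, where imbalance between arms would matter most on the protocol's own reasoning. If the rule were followed literally, these patients could not be randomised, or someone would have to decide case by case which list to use. Patients who fit both B and D would also need someone to choose a list. Either way, judgement enters a procedure meant to have none, and the two-factor stratification claimed in the Discussion is not delivered.

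**Working it through.** No sample size, power or significance level enters this check. It is a matter of logic: apply each definition to each cell of the 2 x 2 table and count the blocks that claim it.

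**Inputs** (Protocol article, Patient allocation and randomization)

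- A: TQ <= 46 and Fletcher Index (FI) < 60 dB
- B: TQ <= 46 and FI >= 60 dB
- C: TQ > 46 and FI < 60 dB
- D as printed: TQ <= 46 and FI >= 60 dB

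**Step 1: compare B and D.** B reads "Patients with a score equal too or less than 46 on the TQ and a Fletcher Index equal to or above 60 dB" and D reads "patients with a score equal to or below 46 on the TQ and a Fletcher Index above or equal to 60 dB". Both say TQ <= 46 and FI >= 60 dB, so the two conditions are identical.

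**Step 2: evaluate the rules on either side of each cut-off.** The last column shows the result if D is read as TQ > 46 and FI >= 60 dB.

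| Example patient | Cell | Blocks as printed | Blocks with D corrected |
|---|---|---|---|
| TQ 46, FI 59 | TQ <= 46, FI < 60 | A | A |
| TQ 46, FI 60 | TQ <= 46, FI >= 60 | B and D | B |
| TQ 47, FI 59 | TQ > 46, FI < 60 | C | C |
| TQ 47, FI 60 | TQ > 46, FI >= 60 | none | D |

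As printed there are three distinct strata against the four announced. With D corrected, every cell maps to exactly one block and the four blocks are exclusive and exhaustive.

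**Step 3: could the missing cell be empty by design?** No. The Participants section admits adults with subjective tinnitus and excludes only those who cannot read and write Dutch; it sets no upper limit on TQ score or hearing loss. The Intervention section provides a separate programme (C) for severely hearing-impaired patients within the level of care meant for moderate to severe complaints. Patients high on both factors are therefore eligible and foreseen.

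**Step 4: is it repaired elsewhere?** No other section gives a definition for TQ > 46 with FI >= 60 dB. The Discussion only restates that both factors are used.

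**Step 5: how many patients?** The article gives no distribution of TQ or Fletcher Index. Assuming that 5% to 15% of the 198 patients fall in the missing cell:

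- 0.05 x 198 = 9.9, about 10 patients
- 0.15 x 198 = 29.7, about 30 patients

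This range illustrates scale only; nothing in the document supports a particular share.

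**The case against.** The strongest reply is that this is a slip in the article and not a fault in the trial. The design is plain: two factors, four blocks, three of them correctly stated, so any reader can work out what D was meant to be. The list existed before the article described it, and the article does not say that the randomiser works from this wording. Randomisation is concealed and done externally, and an operator holding an unused block D list would probably notice the mistake. Even under a literal reading, a patient eligible for both B and D is still randomised, provided the list is chosen without sight of the next allocation. What would suffer there is balance, not randomisation itself. The count of affected patients rests on an assumed share. Adjusting the analysis for the strata could also be seen as a matter for a statistical analysis plan that is not shown.

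Much of this stands as a limit on the consequences. A drafting slip is the likely explanation, nothing shows that any patient was misallocated, and the harm depends on the error having reached the list or the instructions for using it. None of it removes the error. The article chose to state the allocation rule in full and stated one that cannot place an eligible group. That the intended rule can be inferred does not show that it was the rule applied.

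**Conclusion.** The concern holds. The printed rule defines three strata instead of four: one of the four cells is covered twice, and one, TQ above 46 with Fletcher Index of 60 dB or more, is not covered at all. This follows from the text alone and needs no assumption.

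The consequence for the trial is conditional. If the operational list and its instructions use the intended four cells, the fault is confined to the article, and validity is unharmed. If they carry the same error, allocation in two cells was open to ad hoc decisions and balance on both factors is not assured; the number of patients is unknown, about 10 to 30 in the missing cell under the assumed share of 5% to 15%. Inclusion began on 1 September 2007 and the list had already been generated, so patients may already be affected. The list and log should be checked and not presumed correct. As an allocation rule that cannot be carried out as written, it must be corrected.

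**What to change.** 1. Redefine block D as TQ above 46 and Fletcher Index equal to or above 60 dB.
2. Compare the generated list, and any instructions held by the independent randomiser, with the corrected definitions. Go through the log of patients already randomised, confirm the stratum each was drawn from, and record any who were placed by another route.
3. Use the four corrected strata as the stratification factors in the analysis. The Data-analysis section lists tinnitus-related variables among the candidate predictors but lets backward elimination remove every predictor except treatment, so the stratification factors could drop out unless they are fixed in the model.

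The cost is one corrected sentence, one check of the list and log, and a line in the analysis specification. No extra patients are needed, and treatment is unchanged.

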### Intervention

The intervention consists of comprehensive tinnitus management provided by a specialized tinnitus centre in the health care system. The tinnitus centre offers care following a stepped-care approach with two levels (see Fig. 1). Stepped care is a framework for organizing health services based on patients' needs, with a gradual increase in the intensity of the care at each level [16].

The first level of intervention consists of a basic multidisciplinary intervention for all patients referred to TCL. This multidisciplinary intervention consists of audiological diagnostics (Table 1) and intervention, a tinnitus educational group session and an individual consult with a clinical psychologist. For patients with mild complaints this basic multidisciplinary intervention is expected to suffice.

**Table 1 T1:** Audiological diagnostics and intervention in first level

**Audiological diagnostics and intervention**
1. Pure tone and speech audiometry
2. Uncomfortable Loudness Level measurement
3. Tympanometry: including stapedial reflexes
4. Hearing aid check and optimisation (if present)
5. Tinnitus analyses: Pitch Mask Frequency and Masking level
6. Tinnitus anamnesis using structured questionnaire
7. Individual consult by clinical physicist in audiology (60 minutes)

For patients with moderate to severe complaints a second level of intervention exists. This second level of intervention consists of combinations of the following therapies: Cognitive Behavioural Therapy (CBT), Attention Diversion (AD) by means of movement therapy to build up a more positive mind-body relationship, exposure techniques, and Relaxation Therapy (RT). The programs are preferably offered in group format. The group treatments are based on the theoretical framework of the fear-avoidance model proposed by Lethem and colleagues [17], refined by Vlaeyen and Linton [18], and a cognitive behavioural model by Kröner-Herwig [8] explaining factors in the development and maintenance of chronic tinnitus. Based on existing knowledge in chronic pain management, Folmer et al [14] formulated treatment strategies possibly effective for patients suffering from chronic tinnitus, or as they put it, chronic phantom "pain". The authors conclude that severity of depression, anxiety and insomnia is highly correlated with the severity of the tinnitus, similar to chronic pain. They suggest that techniques and strategies effective in treating chronic pain disorder, might be useful in treating tinnitus as well. These include: stress management techniques (including relaxation therapy) to reduce physiological reactivity, cognitive-behavioural techniques to reduce catastrophising cognitions and reduce avoidance behaviours and exposure to fear-eliciting stimuli to adjust for estimations of the tinnitus sound. The treatment under investigation consists of three main programs namely; program A for patients suffering from tinnitus on a moderate to severe level, program B for severe tinnitus complaints, and program C for the severely hearing impaired suffering from tinnitus. All programs are based on the principals stated above. Depending on severity of complaints and hearing loss, group treatment is more intense and tailored to individual needs. In a review from Andersson and Lyttkens [19] it was concluded that offering cognitive behavioural coping techniques in combination with relaxation exercises received the most empirical support.

### Usual Care

Usual care consists of a standardized version of the treatment that is currently applied in peripheral audiological centres throughout the Netherlands for tinnitus patients. A telephone survey was conducted amongst all audiological centres (n = 28) in the Netherlands. The results of this survey determined the content of the usual care treatment protocol in the current study. The treatment consists of audiological diagnostics and intervention and, if necessary, one or more consultations with a social worker with a maximum of ten one hour sessions.

### Outcomes and instruments

Primary outcome measure:

· Generic quality of life, as measured with the Health Utilities Index Mark 3 (HUI3) [20]

Secondary outcome measures:

· Anxiety and depression as measured with the Hospital Anxiety and depression Scale (HADS) [21];

· Tinnitus related disability and handicap, as measured with the Tinnitus Handicap Inventory (THI) [22];

· Tinnitus annoyance and severity, as measured with the Tinnitus Questionnaire (TQ) [15];

· Tinnitus-related fear was assessed by the Fear of Tinnitus Questionnaire (FTQ). This novel 17-item questionnaire is based on the Tampa scale for Kinesiophobia [23] and the Pain Anxiety Symptoms Scale [24];

· Dysfunctional beliefs and/or cognitions regarding the tinnitus, as measured with the Tinnitus Coping and Cognition list (TCCL). The TCCL is a recent adaptation of the Pain Coping and Cognition Questionnaire [25];

· Catastrophic (mis)interpretations of tinnitus, as measured with the Tinnitus Catastrophising Scale (TCS). The TCS is a recent adaptation of the Pain Catastrophising Questionnaire [26];

· Costs, as measured with a retrospective cost questionnaire.

